#### Traits

Relevant traits linked to AUD are of special interest: Impulsivity will be measured with the short questionnaire *Scale for Impulsive Behavior* (I-8 [79]). Sensation seeking will be qualified with the *Need Inventory of Sensation Seeking* (NISS [80])*,* which includes two subscales (need for stimulation and avoidance of rest). To assess *Antisocial Personality Disorder* (ASPD), an adapted questionnaire from the Mini-International Neuropsychiatric Interview (M.I.N.I. [81], also employed in the C-Surf cohort study [82]) will be used. To quantify motivational systems (activation/inhibition), underlying behavior and affect, the *Behavioral Inhibition System/Behavioral Approach System Scales* (BIS/BAS [83]) will be used as in the C-Surf cohort study [84] in a version adapted from the validated German version [85].

#### Other

Additionally, two other measures will be used: experienced emotions as well as the capability of the participant to experience and regulate these emotions will be measured with the *Emo-Check* [86, 87]. The *Trail Making Test A and B* (TMT A & B [88]) screens for neuropsychological executive function by assessing visual attention and task switching. Previous research with preclinical samples indicates that executive functions could influence the relationship between alcohol-related implicit cognitions and addictive behaviors ([89, 90], but see [54]). Consequently, the TMT will be used as a covariate in the statistical analyses.

### Experimental tasks

Both the computerized experimental tasks and response logging are programmed and administered with E-Prime 2.0 (EP2Pro2.0.10.356, Psychology Software Tools, Sharpsburg, PA, USA). With the picture size (344 × 400 pixel) being equal for all three tasks, the set of alcohol-related pictures will be matched to the individual’s drink of choice (beer, wine, or spirits).

#### Go-NoGo Task (GNG)

This task measures response inhibition in both an alcohol-specific and a neutral context. In the modified version of Stein et al. [25], eight pictures of alcoholic beverages (beer, wine, or spirits, according to the participants drink of choice) and eight neutral beverages (water) are presented on screen at a presentation rate of 1 Hz. The pictures are displayed on-screen for 900 ms and the inter-stimulus interval is 100 ms. Participants are instructed to click a button as soon as a stimulus appears on screen (Go trial) unless the same stimulus appears twice in a row (NoGo trial). Each of the 16 pictures will be presented 60 times during the task: 52 times as a Go trial and eight times as a NoGo trial, resulting in a Go/NoGo ratio of 6.5. This ratio is intended to establish a high tendency to respond, making action restraint difficult. In total, the whole experiment thus includes 960 trials (416 neutral Go trials, 416 alcohol-related Go trials, 64 neutral NoGo trials, and 64 alcohol-related NoGo trials), which are presented in a pseudorandomized order, controlling for position, sequential order, and requiring a minimum of two Go trials between two NoGo trials. Half way through, participants are allowed a pause of a self-determined length. The whole task takes approximately 18 min to complete.

#### Stop-Signal Task (SST)

As a second measure of response inhibition, a Stop-Signal Task (SST) will be performed, which includes four pictures of alcoholic beverages located inside a building and four neutral pictures of objects located outside. After a fixation cross, which lasts 460 ms, the individual pictures will appear on a computer screen and participants will be instructed to press the button “a” (left) or “l” (right) as soon as possible to indicate whether the picture was taken inside (confounded with alcohol-related content) or outside a building (confounded with neutral content). During instructions, this pairing of location (inside, outside) and content (alcohol, neutral) is not mentioned. An exception to the rule is to be made when an auditory stop signal occurs (NoGo; 25% of the trials). This stop signal starts with a delay of 100, 200, or 300 ms (each comprising one third of NoGo trials) after stimulus onset. As this stop signal appears after the picture, and not simultaneously with it, as during the GNG or the training, task performance in the SST depends on action cancellation and thus measures a slightly different aspect of response inhibition. After completion of two practice blocks each, two test blocks comprising 240 trials each (180 Go and 60 NoGo trials) will be completed. The key allocation is counterbalanced, and the order of trials is pseudorandomized. As an indicator of response inhibition, the stop-signal reaction time (SSRT) will be computed for alcohol-related and non-alcoholic pictures according to the algorithm described in Houben, Havermans [32].

#### Implicit Association Test (IAT)

Implicit associations between alcohol and affective attributes will be measured with an alcohol-specific IAT [91]. In a *valence IAT*, pictures of alcoholic beverages are either paired with a positive (e.g., funny) or a negative (e.g., dull) word. Participants must classify if a stimulus either belongs to one of the target categories (pictures of alcoholic drinks vs. waters) or to one of the affective categories (positive vs. negative verbs) with response buttons on a keyboard (left “a” vs. right “l”). The eight alcoholic and eight water pictures are the same as in the inhibition training (see “Stimulus material”). In accordance with previous preclinical studies [32, 33], the affective categories consist of eight positive (happy, jolly, energetic, funny, sociable, attractive, cheerful, smart) and eight negative (dull, miserable, sick, depressed, unhappy, disgusting, angry, foolish) attributes. The German translation (glücklich, ausgelassen, dynamisch, lustig, gesellig, attraktiv, fröhlich, klug, lustlos, miserabel, übel, deprimiert, unglücklich, widerlich, wütend, dumm) were validated by three independent native-English speakers. During “alcohol-positive” blocks, stimuli from the categories alcohol and positive are represented by one response button, while water and negative attributes require pressing the other response button. Contrary to this, during “alcohol-negative” blocks, stimuli from the alcohol and negative category share one response button, while water and positive attributes are indicated with the other response button. Based on the rationale that associated concepts (e.g., alcohol and positive attributes) are more easily combined than unrelated concepts (e.g., alcohol and negative attributes), reaction time differences between these two blocks can be used to assess the association strength between target and affective categories. According to the developers [91], a significant difference in reaction time between both examples would indicate strong positive associations towards alcohol.

For this study, task development in E-Prime was based on an adapted version used by Egenolf et al. [92]. To control for sequence effects of the starting target concepts (alcohol, water) both IAT versions consist of 14 blocks. All blocks are interposed with rest periods of a self-determined length. Initially, and whenever key assignment changes, participants will undergo two or three practice blocks consisting of 16 trials each: First, they classify the target concepts (alcohol, water) and/or the affective categories (positive, negative) to left (“a”) and right (“l”). Second, they practice the combination of target concepts and affective categories. After these blocks, a longer test block of 64 trials follows (for an overview of the procedure, see Additional file 3). To remind participants of the current mapping rule, category labels will be presented in the upper two corners of the screen. Stimuli will appear on-screen for maximum 1750 ms or until an answer is given, followed by feedback (for 200 ms). The interstimulus interval will be 250 ms. The IAT consists of 416 trials and lasts 10–20 min depending on the individual’s speed and duration of rest periods. Reaction time analyses will be conducted according to the improved scoring algorithm by Greenwald, Nosek et al. [93].

### Procedure patients

The study duration from the admission of the first participant to the last participant’s follow-up is 36–40 months. The duration of participation for an individual study participant is commonly 14–16 months depending on the duration of the inpatient stay. Apart from the main study, the substudies *cortisol* and *EEG* are integrated in the main study procedure. During the standard inpatient treatment, the assessments T1 to T4 will take place. After discharge, and at each of the three follow-up time points, questionnaires will be sent to each participant, and they are additionally contacted by telephone (see also Fig. 1). For an overview about the single time points, consult the Standard Protocol Items: Recommendations for International Trials (SPIRIT) Figure (Fig. 2). The SPIRIT Checklist is also provided as Additional file 4.

**Fig. 2 Fig2:**
[figure not shown]
Enrollment, interventions and assessments at each time point for patients in the INTRA study. A schematic outline of the enrollment, interventions and assessments that each participant of the main INTRA study will undergo. *AASE-G* Alcohol Abstinence Self-efficacy Scale – German version, *Alc-IT* alcohol-inhibition training, *ASPD* antisocial personality disorder, *ASRS-V1.1* Adult ADHD Self-Report Scale, *AUDIT* Alcohol Use Disorders Identification Test, *AUD-S* Alcohol Use Disorders Scale, *BAI* Beck Anxiety Inventory, *BDI-ll* Beck’s Depression Inventory, *BIS/BAS* Behavioral Inhibition System/Behavioral Approach System Scale, *BSCL* Brief Symptom Check List, *CAEQ* Comprehensive Alcohol Expectancy Questionnaire; Craving (Likert scales), *DIA-X* Diagnostic Expert System for Psychiatric Disorders, *Emo-Check* Assessment of Emotion and Emotion regulation, *GNG* Go-NoGo Task, *HDL* Health and Daily Living Form, *IAT* Implicit Association Test, *IT* inhibition training, *I-8* Scale for Impulsive Behavior, Motivation (Likert scales), *NISS* Need Inventory of Sensation Seeking, *OCDS-G* Obsessive Compulsive Drinking Scale – German version, *PSS* PTSD Symptom Scale, *SCI* Stress and Coping Inventory, *SOCRATES* Stages of Change Readiness and Treatment Eagerness Scale, *SST* Stop-Signal Task, *TLFB* Timeline Follow-back, *TMT* Trail Making Test A and B*, WHOQOL-BREF WHO Quality of Life Scale (brief version), −T1* before treatment admission, *T1* baseline, *T2* pre-training, T3 post training, *T4* discharge, *T5* 3-month follow-up, *T6* 6-month follow-up, *T7* 12-month follow-up

#### Recruitment

At treatment admission, all patients’ medical records will be screened for eligibility for participation in the study. If all inclusion criteria and no apparent exclusion criteria are fulfilled, the patient will be invited to an information appointment during the first treatment week. Therein, the study will be explained, questions will be answered, and lastly, the person is asked if they would participate. For those having given informed consent, we will screen for other severe substance use disorders using the DUDIT [47].

#### T1: Inclusion and baseline assessment

During the second treatment week, a member of the study team will conduct an interview to confirm the AUD diagnosis (DIA-X adapted to DSM-5 criteria; [55]). To assess the drinking quantity of the 90 days prior to detoxification, the TLFB interview will be conducted [59, 60]. Furthermore, a psychological assessment with a test battery consisting of questionnaires will also take place at this time point.

#### Randomization and blinding

Patients will be randomly assigned to one of the three study arms, with the aim of generating equally sized groups. Block randomization with variable block sizes will be stratified according to gender and age (age groups: 18–25, 26–35, 36–45, 46–55 and 56–60 years). The stratified randomization list will be generated with Matlab (Version 2017a, MathWorks, Inc., Natick, MA, USA), and stored in one document. The participants’ allocation to a study arm will be done by an independent investigator who will administrate and conceal the list. Thus participants, investigators, care providers and members of the study team will be blind to the allocation schedule.

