**Methods:**

This is a double-blind, randomized controlled trial (RCT) with 246 inpatients with AUD participating. After baseline assessment, participants are randomly assigned to one of three computerized Go-NoGo-based inhibition training interventions (two alcohol-specific versions with different Go/NoGo ratios, or neutral control training) and one of two intervention times (morning/afternoon), resulting in six study arms. All patients perform six training sessions within 2 weeks. Endogenous cortisol is measured in 80 patients before and after the first training session. Inhibitory control and implicit associations towards alcohol are assessed pre and post training, at which point electroencephalography (EEG) is additionally measured in 60 patients. Patients’ alcohol consumption and relevant psychological constructs (e.g., craving, self-efficacy, treatment motivation) are measured at discharge and at 3-, 6- and 12-month follow-ups. Fifty healthy participants are assessed (20 with EEG) at one time point as a healthy control group.

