#### Main study

Training effects on our primary outcome measures (PDA and HDD at 3-month follow-up) will be assessed with a 2 × 3 analysis of variance (ANOVA) with the factors time point (T1, T5) and training group (Alc-IT (50/50), Alc-IT (75/25) or control). Further, a Cox regression will be computed to predict the effect of the intervention on TFD (at 3-month follow-up).

Training effects on experimental test parameters will be assessed with a 2 × 2 × 3 repeated measures ANOVA with the factors measurement point (T2, T3), time of day (morning, afternoon) and training group (Alc-IT (50/50), Alc-IT (75/25) or control). Where Mauchly’s test of sphericity indicates heterogeneity of covariance, we will verify repeated measures results with Greenhouse-Geisser corrections.

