### Power calculation

The intended sample size was calculated with G*Power (Version 3.1.5, Heinrich-Heine-University Duesseldorf, Dusseldorf, Germany). In a-priori analyses (1−β = 0.8, α = 0.05), slightly reduced expected effect sizes were entered compared to earlier studies because of the additional manipulations concerning different training versions and time of training. For the 2 × 3 ANOVA to examine the training effects on the primary outcome measures PDA and HDD (with an expected effect size of f = 0.2 based on earlier studies [32]), a total sample size of *n* = 244 is needed. For the analyses of the training’s effect on TFD (the third primary outcome, estimating a small to medium effect size of w = 0.25 based on earlier studies [37], and df = 3), G*Power indicated a total sample size of *n* = 174 for the Cox regression. For the 2 × 2 × 3 repeated measures ANOVA examining training effects on experimental parameters and also taking into account the effects of time of day of the training (expecting small to medium effects of f = 0.15 and correlations of 0.4 among repeated measures based on earlier studies [107]), the necessary sample size was *n* = 180. Considering the necessary power for all analyses and similar sample sizes in all study arms (82 per intervention group), a total of 246 patients will be recruited.

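### The primary PDA/HDD ANOVA omits the stratification factors and time of day, no stated drinking analysis contains time of day, and the text gives both three and six randomised arms

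*Protocol article*

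**What the plan says.** All references are to the protocol article.

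- **Randomization and blinding:** "Patients will be randomly assigned to one of the three study arms", and "Block randomization with variable block sizes will be stratified according to gender and age". There are five age bands, so 2 × 5 = 10 strata. Time of day is not mentioned.
- **Abstract, Methods:** patients are randomised to a training version and to "one of two intervention times (morning/afternoon), resulting in six study arms". Study design and setting also counts six conditions.
- **Statistics, Main study:** PDA and HDD are analysed by a 2 × 3 ANOVA whose two named factors are time point (T1, T5) and training group. For TFD: "Further, a Cox regression will be computed to predict the effect of the intervention on TFD". No covariates are listed for it. Time of day is a factor only in the 2 × 2 × 3 ANOVA on the experimental tasks.
- **Study aim:** the effect of time of training on training efficacy is to be investigated.
- **Interviews and questionnaires, Other:** "Consequently, the TMT will be used as a covariate in the statistical analyses". No model is named for it.
- **Power calculation:** "In a-priori analyses (1−β = 0.8, α = 0.05), slightly reduced expected effect sizes were entered"; for PDA and HDD, "with an expected effect size of f = 0.2 based on earlier studies", so that "a total sample size of *n* = 244 is needed". Recruitment is set at 246.

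**The concern.** Stratified blocks balance gender and age across the training groups. If those factors predict the outcome, an analysis that ignores them leaves their variance in the error term although randomisation has removed it from the group comparison. The reported standard error is then larger than the true one, the test rejects too rarely under the null, and power is lost. In a Cox model, omitting prognostic factors pulls the hazard ratio toward 1.

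Time of day raises a separate problem. It is described as a randomised factor and a study aim, yet the models for the primary outcomes do not contain it, so the plan as written cannot answer that question for drinking. Moreover, the randomisation section does not mention it. Whether the morning/afternoon comparison is a randomised one therefore depends on which section is right.

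**Working it through.** **1. The plan's own figure.** Inputs from Power calculation: f = 0.2, α = 0.05, three groups, numerator df 2. Noncentrality is λ = N·f².
- N = 244: λ = 244 × 0.04 = 9.76, power 0.800. The stated 244 reproduces.
- N = 246: λ = 246 × 0.04 = 9.84, power 0.804.

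**2. Which variance counts.** With two time points, the time point × group test is a one-way F test on the change from T1 to T5. Gender or age effects of equal size at both time points cancel. The relevant R² is therefore the share of variance in *change* that gender and age explain. The documents do not give it; 0 to 0.20 is assumed.

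**3. Effect of adjusting the ANOVA.** Gender takes 1 df and age 4. Adjusted λ = 9.84/(1 − R²), denominator df 246 − 3 − 5 = 238. The standard-error ratio (adjusted to unadjusted) is about √(1 − R²). Approximate type I error of the unadjusted test is P(F > 3.033/(1 − R²)) on (2, 243) df, where 3.033 is the 5% critical value.

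| R² (change) | λ adjusted | Power adjusted | √(1 − R²) | Simulated SE ratio | Type I error, unadjusted |
|---|---|---|---|---|---|
| 0 | 9.84 | 0.804 | 1.000 | 1.002 | 0.050 |
| 0.05 | 10.36 | 0.825 | 0.975 | 0.975 | 0.043 |
| 0.10 | 10.93 | 0.846 | 0.949 | 0.950 | 0.036 |
| 0.20 | 12.30 | 0.887 | 0.894 | 0.894 | 0.024 |

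The simulated ratios come from 2,000 runs per setting with 10 strata, permuted blocks and N = 246. At R² = 0.10 the simulated type I error was 0.031.

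**4. Time of day in the ANOVA.** With six cells (3 versions × 2 times) and N = 246, power for the training effect is still 0.804, so including the factor and its interaction costs nothing visible. For the training × time-of-day interaction on (2, 240) df:
- f = 0.10: λ = 246 × 0.01 = 2.46, power 0.27
- f = 0.15: λ = 246 × 0.0225 = 5.54, power 0.54
- f = 0.20: λ = 9.84, power 0.80

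**5. Cox model.** Simulation assumptions, none from the documents: 50% relapse in controls by day 90, hazard ratio 0.6 for both active versions, and gender/age effects with SD 0.3 or 0.6 on the log-hazard scale; 1,200 runs per setting. The true log hazard ratio is −0.511.

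| SD of strata effect | Log HR unadjusted | Log HR adjusted | Model SE unadjusted | Model SE adjusted |
|---|---|---|---|---|
| 0.3 | −0.494 | −0.513 | 0.245 | 0.247 |
| 0.6 | −0.466 | −0.521 | 0.241 | 0.243 |

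Adjustment removes attenuation (hazard ratio 0.63 back to 0.59 with the strong effect) but does not narrow the interval. With age as five categories, 34 and 135 of the 1,200 runs in these two settings failed to converge and were dropped, because some age groups were sparse.

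**6. Text comparison.** The abstract and Study design and setting give six randomised arms or conditions. Randomization and blinding gives three. The first reading makes the morning/afternoon contrast randomised; the second does not say how the time slot is assigned.

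**The case against.** - **Size and direction.** The loss depends entirely on an R² that the documents do not give. At R² = 0.02 adjusted power is 0.812, almost no gain. The error is always conservative, so it creates no false-positive risk. This stands. A reader might infer that the intervals *are* too wide; the documents support only that they may be. Leaving out a balanced time-of-day factor widens nothing unless time of day affects drinking.
- **Cox model.** A reader might infer that the Cox model excludes the stratification factors. The text neither lists nor excludes covariates. The power calculation uses df = 3 for TFD, one more than three training groups need, so a time-of-day term may even be intended. An omission cannot be shown.
- **Detail left to the analysis plan.** Covariate lists are often placed there, and that plan is not shown. This answers the Cox model and the TMT, whose absence from the model description is not proof of a broken commitment. It does not answer the ANOVA, which is given as a closed two-factor model directly beside one that does include time of day.
- **Time of day.** The first research question compares active training with control only, and time of day is analysed for the experimental tasks. But the aim refers to training efficacy generally, and drinking is the primary outcome. A reader might also infer that slots follow the clinic timetable. Nothing says so: the abstract randomises time of day, and Training (intervention) lists it next to the allocated version.
- **Site.** It is not a stratification factor, so adjusting for it is a preference.

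**Conclusion.** The point holds in a limited form. The primary PDA/HDD ANOVA is fixed without gender, age or time of day, and the Cox model states no covariates. For an assumed R² of 0 to 0.10 in change, the efficiency at stake is 0 to about 5% of the standard error and 0 to about 4 percentage points of power (80.4% to 84.6%). At R² = 0.20 it is about 11% and 8 points. For TFD the possible cost is attenuation of the hazard ratio, and only if the strata are prognostic.

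Two parts do not depend on R²: the time-of-training aim has no stated analysis on the drinking outcomes, and the article gives both three and six randomised arms. These justify a change even if adjustment gains nothing.

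**What to change.** 1. Add gender, age group and time of day, and the TMT as already promised, to the PDA, HDD and TFD models. In the Cox model, enter age as continuous or merge sparse age groups.
2. Name training × time of day as a secondary test for drinking, and state its limited power: about 27% at f = 0.10 and 54% at f = 0.15.
3. Reconcile the three arms in Randomization and blinding with the six in the abstract and in Study design and setting. If time of day was not on the randomisation list, report that comparison as non-randomised. Say what the df = 3 for TFD stands for.
4. Adjustment for site is optional.

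Cost: gender 1 + age 4 + time of day 1 + TMT 1 or 2 + interaction 2 = 9 or 10 degrees of freedom out of 246. Every variable is already collected or known for each patient. The main analyses are scheduled for after data collection, which the article reports as ongoing, so the models can be fixed before treatment effects are seen.
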